## Abstract

**Background:**

Acupuncture is beneficial for controlling chemotherapy-induced nausea and vomiting (CINV). However, the effect of different acupoint combinations on controlling CINV remains unknown. This study aims to compare the effects of distal-proximal point association and local distribution point association on controlling CINV.

**Methods/design:**

The study is a single-center, randomized controlled trial. A total of 240 participants will be randomly divided into four groups. The control group will receive standard antiemetic only, whereas three acupuncture groups will receive four electro-acupuncture treatments once a day with the standard antiemetic. Acupuncture group I and II will receive distal-proximal point association (“Neiguan (PC6) and Zhongwan (CV12)”, and “Zusanli (ST36) and CV12”, respectively); Acupuncture group III will receive local distribution point association (“Shangwan (CV13) and CV12”). The primary outcome measures are the frequency and distress of nausea and vomiting. The secondary outcome measures are the grade of constipation and diarrhea, electrogastrogram, quality of life, etc. Assessment is scheduled from the day before chemotherapy to the fifth day of chemotherapy. Follow-ups are performed from the sixth day to the twenty-first day of chemotherapy.

**Discussion:**

Results of this trial will help in evaluating the efficacy and safety of electro-acupuncture with different acupoint combinations in the management of CINV.

**Trial registration:**

ClinicalTrials.gov identifier: NCT02478047.

## Background

Chemotherapy-induced nausea and vomiting (CINV) are common side-effects of many antineoplastic regimens and can occur for several days after treatment [1]. CINV significantly impacts the patient’ quality of life and nutritional status, and may lead to dose reduction or treatment discontinuation, subsequently increasing the risk of disease progression [2]. Although effective guidelines for CINV prevention exist for both moderately and highly emetogenic chemotherapies, adherence to these guidelines is not widely practiced because of their expensive costs and side-effects, such as headaches, dizziness, constipation, and insomnia [1].

Acupuncture treatment is one of the most sought-after therapeutic modalities in complementary and alternative medicine [3]. It is a safe medical procedure with minimal side effects. Evidence for the therapeutic effects of acupuncture on CINV exists [4]. Electroacupuncture for CINV management has been recommended by the American Society of Clinical Oncology [5]. Based on Traditional Chinese Medicine (TCM), the combination of acupoints can strengthen the essential and comprehensive therapeutic effects of acupuncture [6]. However, no consensus currently exists on the optimal acupoint combination for controlling CINV. For example, Gottschling S [7] found that stimulating PC6 (Neiguan), CV12 (Zhongwan), ST36 (Zusanli) and LI4 (Hegu) may effectively prevent CINV; Shen J [8] concluded that electro-acupuncture on PC6 (Neiguan) and ST36 (Zusanli) is more effective in controlling emesis than antiemetic pharmacotherapy alone. Therefore, we propose a randomized, controlled trial to determine the optimal combination of acupoints for CINV management.

In this trial, we aim to determine whether different acupoint combinations similarly manage CINV. We also aim to determine whether distal-proximal point association or local distribution point association more efficiently manages CINV.

## Methods/design

### Objectives

This study aims to: (1) assess the clinical efficacy and safety of distal-proximal point association and local distribution point association by electro-acupuncture for CINV management; (2) assess the patients’ quality of life, anxiety, and depression, as well as other side effects of chemotherapy, such as diarrhea and constipation.

### Hypothesis

According to the theory of TCM, the combination of acupoints can achieve a synergistic effect. In addition, distal-proximal point association and local distribution point association are the classic methods for combinating acupoints. We hypothesize that distal-proximal point association will achieve better therapeutic effect by reducing toxicity and enhance efficacy in CINV management.

### Design

This is a four-armed parallel randomized controlled trial (RCT). 240 participants will be randomly assigned to four groups (a control group and three acupuncture groups) through central randomization in a 1:1:1:1 ratio. The flow chart is shown in Fig. 1.

**Fig. 1 Fig1:**
[figure not shown]
Flow chart of the study

### Recruitment

All participants will be recruited from the Tianjin Medical University Cancer Institute and Hospital, and the clinical trial information will be posted on notice boards of the hospital. Our trial started on June 2015, and the first participant was recruited on 26 June 2015. For eligible participants who meet all required criteria, it will be requested to sign the written informed consent before randomization, meanwhile they will be given enough time to decide whether they willing to join this study.

### Inclusion and exclusion criteria

#### Inclusion criteria

Participants who meet all of the following criteria will be considered for enrollment. The inclusion criteria are as follows: (1) Diagnosed with cancer and need chemotherapy. (2) The score of Karnofsky (KPS) ≥ 70. (3) Between 18 and 80 years old (either sex). (4) Receiving chemotherapy as outpatients or inpatients. (5) Receiving chemotherapy for one or multiple cycles, but the patient will be taken into the study only once. (6) Patients receiving chemotherapy containing cis-platinum (cis-platinum ≥ 75 mg/m^2^) or antharcycline-combined chemotherapy (doxorubicin ≥ 40 mg/m^2^ or epirubicin ≥ 60 mg/m^2^). (7) Life expectancy ≥ 6 months. (8) Willing to participate in the study and be randomly allocated into one of the four study groups.

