#### Exclusion criteria

Participants who meet any of the following will be excluded: (1) Receiving radiotherapy concurrently with chemotherapy. (2) Gastrointestinal tumors. (3) Liver disease with serious complications, or with serious abnormal hepatorenal function (glutamic oxalacetic transaminase (AST), glutamic-pyruvic transaminase (ALT), or total bilirubin (TBIL) three times higher than normal, blood urea nitrogen (BUN) or urine creatinine (Cr) two times higher than normal). (4) Presence of cardiac pacemaker. (5) Active skin infection. (6) Nausea and/or vomiting resulting from opioids or metabolic imbalances, such as electrolyte disturbances. (7) Unable to provide self-care or communicate, or have mental illness. (8) Nausea and/or vomiting resulting from mechanical risk factors, such as, intestinal obstructions. (9) Brain metastases or intracranial hypertension. (10) Pregnant or lactating.

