### Participant timeline

Enrollment will be conducted the day before chemotherapy (day 0). The electro -acupuncture intervention will be given once daily from day 1 to day 4. The schedule of enrollment, interventions, and assessments is shown in Table 2.

**Table 2 Tab2:** The schedule of enrollment, interventions, and assessments

	Study period								
	Enrolment	Allocation	Post-allocation						Close-out
Time points	-t1	t0	t1	t2	t3	t4	t5	t6-t20	t21
Enrollment									
Eligibility screen	√								
Informed consent	√								
Allocation		√							
Interventions									
Control group									
Experimental group I			√	√	√	√			
Experimental group II			√	√	√	√			
Experimental group III			√	√	√	√			
Assessments									
Baseline variables	√	√							
The frequency of nausea and vomiting		√	√	√	√	√	√	√	√
The grading of nausea and vomiting		√	√	√	√	√	√	√	√
Rhodes Index of nausea, vomiting and retching		√	√	√	√	√	√	√	√
The grading of constipation and diarrhea		√					√		√
eletrogastrogram		√					√		√
quality of life		√					√		√
anxiety and depression		√					√		√
Other adverse effect during the chemotherapy							√		√
The adverse effects of acupuncture			√	√	√	√			

t0, the day before chemotherapy; t1-t5, the first day to the fifth day of chemotherapy; t6-t21, the sixth day to the 21st day of chemotherapy

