### Outcome measures

The observation period will cover the day before chemotherapy (day 0) to the fifth day of chemotherapy (day 5). Follow-ups will be conducted from the sixth day (day 6) to the twenty first day (day 21) of chemotherapy. Participants will be asked to keep CINV diaries from the sixth day (day 6) to the twentieth day of chemotherapy (day 20).

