#### Primary outcome measures

The primary outcome measures are as follows:Frequency of nausea and vomiting: total nausea and vomiting episodes per person over the 6-day study period will be recorded. The frequency of nausea and vomiting is the most valuable measurement for evaluation.Grading of nausea and vomiting: nausea and vomiting will be graded by Common Terminology Criteria for Adverse Events Version 4.0 [12].Rhodes Index of Nausea, Vomiting and Retching: nausea, vomiting and retching will be measured as separate entities by Rhodes Index of Nausea, Vomiting and Retching, which have 8 items with 5-point Likert scales. The frequency and distress of all entities are measured, as well as the duration of nausea and the amount of vomitius. [13]

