### Statistical analysis

Statistical analysis will also be performed by the Clinical Evaluation Center at China Academy of Chinese Medical Science. The statistician is blinded from the allocation of groups. The Kruskal-Wallis test will be employed in the analysis of skewed distribution data. Chi-square analysis will be used for categorical variables, and Analysis of variance (ANOVA) for numerical variables. Repeated measures analysis will be used in the different time point assessment. A *P* value less than 0.05 is regarded as statistically significant.

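### Any-cycle entry combined with exclusions by named cause lets patients with nausea or vomiting already present before this cycle into the trial, and their episodes enter the primary total

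*Protocol article*

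**What the plan says.** Inclusion criterion (5) of the protocol article reads "Receiving chemotherapy for one or multiple cycles, but the patient will be taken into the study only once". Criterion (6) requires a cisplatin or anthracycline regimen, so someone entering at a later cycle may already have been through such treatment.

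Two exclusions deal directly with existing symptoms, and both work by cause: criterion (6), "Nausea and/or vomiting resulting from opioids or metabolic imbalances, such as electrolyte disturbances", and criterion (8), "Nausea and/or vomiting resulting from mechanical risk factors, such as, intestinal obstructions". Criterion (9) removes brain metastases and intracranial hypertension. Criteria (1) and (2) remove concurrent radiotherapy and gastrointestinal tumours. No criterion mentions anticipatory symptoms, symptoms persisting from a previous cycle, or a symptom-free interval before chemotherapy.

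For the first primary outcome, "total nausea and vomiting episodes per person over the 6-day study period will be recorded". The Outcome measures section sets the observation period as day 0 to day 5. The note to Table 2 defines the days: "t0, the day before chemotherapy; t1-t5, the first day to the fifth day of chemotherapy". The acupuncture "intervention will be given once daily from day 1 to day 4".

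The Randomization section has eligibility checked first, then the allocation obtained, and only then a baseline evaluation by the evaluator. Table 2 ticks frequency, grading and the Rhodes Index at t0, in the allocation column.

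**The concern.** The exclusions show an intention to keep out emesis that the current chemotherapy did not cause. Yet the list omits the kind of pre-existing symptom that any-cycle entry itself brings in. A patient in a later cycle who is vomiting on day 0, from anticipation or from the previous cycle, meets every criterion.

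The primary count then takes in that patient's episodes. Those on day 0 come before both the chemotherapy and the first acupuncture session. Those that continue on day 1 and later cannot be told apart from new ones. Starting the count at day 1 would remove the first kind but not the second.

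At stake is how precisely and cleanly the arms can be compared, above all distal-proximal against local point association, which is the trial's stated hypothesis.

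**Working it through.** **1. Eligibility.** Take a patient in a later cycle who is nauseated on day 0 and has none of the named causes. Inclusion (5) is met. Exclusions (6), (8) and (9) do not apply. The patient is eligible.

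**2. Counting window.** Day 0 to day 5 is 5 − 0 + 1 = 6 days, which matches the 6-day period in the primary outcome. One of the six days precedes chemotherapy and treatment.

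**3. Sample size.** The plan's own inflation reproduces: 192 / (1 − 0.20) = 240, or 60 per arm, with 192 / 4 = 48 evaluable per arm. The 192 itself cannot be reproduced, because the article gives no effect size or variance.

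**4. Chance imbalance.** Let p be the share of patients with day-0 symptoms. The document gives no value, so p = 10%, 20% and 30% are assumptions. Arms are taken as independent binomials of size 60, and the event is a gap of 10 points or more in either direction.

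- One distal-proximal arm against the local arm: SE = √[p(1 − p)(1/60 + 1/60)]. Ten points is 6 patients of 60, so with a continuity correction z = (5.5/60)/SE.
- Both distal-proximal arms pooled (120) against local (60): SE = √[p(1 − p)(1/120 + 1/60)]. Ten points is 12 patients of 120, so z = (11.5/120)/SE.

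| p | SE, one pair | z | Chance | SE, pooled | z | Chance |
|---|---|---|---|---|---|---|
| 10% | 0.0548 | 1.67 | 9% | 0.0474 | 2.02 | 4% |
| 20% | 0.0730 | 1.26 | 21% | 0.0632 | 1.52 | 13% |
| 30% | 0.0837 | 1.10 | 27% | 0.0725 | 1.32 | 19% |

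Exact binomial sums give the same rounded percentages. For cycle status, if half the patients were in a later cycle (also an assumption), the same formulas give 32% for one pair and 23% pooled.

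**5. Added variance, illustration only.** With 48 per arm, two-sided 5% (the sidedness is not stated) and 90% power, the detectable standardised difference for two means is (1.960 + 1.282) × √(2/48) = 0.662. Suppose pre-existing symptoms, unaffected by treatment and not allowed for in planning, make up a share v of the outcome variance. Power is then Φ(0.662 × √(1 − v) / √(2/48) − 1.960):

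| v | Power |
|---|---|
| 5% | 88.5% |
| 10% | 86.8% |
| 20% | 82.6% |
| 30% | 77.4% |

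The shares are assumed; nothing in the document fixes them.

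**The case against.** **Any-cycle entry is a deliberate choice.** The criterion is explicit and bars re-entry, and it can be defended on generalisability. The objectives speak of CINV management and do not restrict it to patients who start symptom-free. This stands, and the fix keeps any-cycle entry. What it does not answer is why the list removes other prior causes and leaves this one.

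**The symptoms are measured.** Table 2 records them at t0, and "Repeated measures analysis will be used in the different time point assessment". An analysis plan that is not shown could adjust for day 0 and for cycle. That stands in part: adjustment can recover precision. It does not change who is enrolled, and it does not turn anticipatory or left-over episodes into symptoms of this cycle.

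**The variance may already be allowed for.** The sample size drew on a pilot study. If the pilot enrolled similar patients, some or all of the loss in step 5 is already inside the 192. The article does not say.

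Four stronger readings are tempting, and the document does not support them:

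- *The comparison is biased.* Randomization makes pre-existing symptoms equally likely in every arm. A chance imbalance is part of what the type I error already covers.
- *Randomization leaves cycle status unbalanced.* The article gives the 1:1:1:1 ratio and the central web system and says nothing either way on stratification or blocking, which a condensed article may leave to the full protocol.
- *The imbalance risk is 33 to 69%.* That is the chance that the widest gap among all four arms reaches 10 points under the same assumed prevalences. It includes pairs without the local arm, so it is not the risk for the distal-proximal against local comparison.
- *Sites will judge cause differently.* The trial is single-center. Staff within it may still differ, but judging cause is ordinary eligibility practice.

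**Conclusion.** The gap is real and lies in what the criteria say. Patients with nausea or vomiting before this cycle, from anticipation or from an earlier cycle, are eligible, and their episodes count in the primary total. The harm is dilution, added variance and chance imbalance.

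The size depends on a prevalence that the document does not give. At an assumed 10 to 30%, a gap of 10 points or more has a chance of about 9 to 27% for one distal-proximal arm against local and about 4 to 19% for the pooled comparison. How far such a gap would move the outcome is unknown. The trial remains interpretable without the change, but its main count would measure control of this cycle's symptoms less cleanly. The point should be addressed; it does not undermine the design.

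**What to change.** 1. Add an exclusion that does not depend on cause: any vomiting or retching, or nausea above a stated CTCAE or Rhodes level, in the 24 hours before chemotherapy.
2. Move the day-0 symptom check in Table 2 ahead of the randomization call, and amend the Randomization section, which now places baseline evaluation after allocation. Because allocation falls on day 0, word the interval so that it closes at this check; otherwise some patients would be excluded after allocation.
3. Keep any-cycle entry.
4. For patients already enrolled, use the day-0 measure and cycle status (first versus later) as covariates. Day 0 is already collected; cycle status has to be recorded if it is not.

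**Cost.** Recruitment slows slightly, and the population narrows to patients without material symptoms at the start. Recruitment is under way, so eligibility would change mid-trial, and the change and its date must be reported. Anticipatory symptoms that first appear after the check would still be counted.

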#### Exclusion criteria

Participants who meet any of the following will be excluded: (1) Receiving radiotherapy concurrently with chemotherapy. (2) Gastrointestinal tumors. (3) Liver disease with serious complications, or with serious abnormal hepatorenal function (glutamic oxalacetic transaminase (AST), glutamic-pyruvic transaminase (ALT), or total bilirubin (TBIL) three times higher than normal, blood urea nitrogen (BUN) or urine creatinine (Cr) two times higher than normal). (4) Presence of cardiac pacemaker. (5) Active skin infection. (6) Nausea and/or vomiting resulting from opioids or metabolic imbalances, such as electrolyte disturbances. (7) Unable to provide self-care or communicate, or have mental illness. (8) Nausea and/or vomiting resulting from mechanical risk factors, such as, intestinal obstructions. (9) Brain metastases or intracranial hypertension. (10) Pregnant or lactating.

### Randomization

After signing an informed consent and evaluating the inclusion and exclusion criteria, participants will be randomly assigned to one of four groups by center randomization. The central randomized system will be used and performed by the Clinical Evaluation Center at China Academy of Chinese Medical Science in Beijing. A random number and group assignment will be immediately obtained through the website at http://118.144.35.11/crivrs/index.htm. Then the practitioner will assign the participant to that intervention and the evaluator will perform a baseline evaluation.

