### Blinding

The evaluator and the statistician are blinded to the intervention a participant accepts. Acupuncturists and patients are not blinded to the treatments they deliver because of the nature of the intervention.

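### The baseline evaluation is placed after allocation although patients know their arm; the day-0 outcome measures should be completed before the assignment is obtained

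*Protocol article*

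**What the plan says.** All references are to the protocol article.

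- **Randomization**, before allocation: "After signing an informed consent and evaluating the inclusion and exclusion criteria, participants will be randomly assigned to one of four groups". Only consent and eligibility are named as preceding it.
- **Randomization**, the allocation itself: "A random number and group assignment will be immediately obtained through the website".
- **Randomization**, the next step: "Then the practitioner will assign the participant to that intervention and the evaluator will perform a baseline evaluation".
- **Blinding**, evaluator: "The evaluator and the statistician are blinded to the intervention a participant accepts".
- **Blinding**, patients: "Acupuncturists and patients are not blinded to the treatments they deliver because of the nature of the intervention".
- **Participant timeline**: enrolment takes place on day 0. The footnote to Table 2 begins "t0, the day before chemotherapy; t1-t5, the first day to the fifth day of chemotherapy". Allocation is ticked at t0. The rows for frequency and grading of nausea and vomiting, Rhodes Index, quality of life, and anxiety and depression are all first ticked at t0, and none at -t1. Only the generic row for baseline variables has a tick at -t1, and it is ticked again at t0.
- **Primary outcome measures**: "total nausea and vomiting episodes per person over the 6-day study period will be recorded". The Outcome measures section defines the observation period as day 0 to day 5.
- **Statistical analysis**: a repeated measures analysis is planned across time points. The role of t0 in it is not stated.

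**The concern.** A baseline is useful because allocation cannot have influenced it. Here the stated order gives up that property. Rhodes Index, FACT-G and Hospital Anxiety and Depression Scale answers come from the patient. On the eve of chemotherapy, learning that one will receive antiemetics only, or electro-acupuncture as well, can plausibly change how anxiety, well-being and even nausea are reported. The evaluator's blinding protects the recording of the answers, not the answers.

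Lack of patient blinding during treatment is unavoidable in this design. A baseline taken after assignment is avoidable. It also cannot be repaired by an analysis plan, because a pre-allocation value that was never collected cannot be recovered.

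**Working it through.** **Step 1: order of events.** Read in sequence, the Randomization section gives: consent and eligibility; random number and group obtained at once from the website; practitioner assigns the participant; evaluator performs the baseline evaluation. Table 2 cannot reverse this, because allocation and the first outcome assessments share one column. The order within t0 therefore rests on the Randomization section alone, and baseline comes last there. No section says that the assignment is withheld until the baseline is complete.

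**Step 2: does day 0 reach the primary count?** Day 0 to day 5 is 5 − 0 + 1 = 6 days, which matches the six-day period of the primary frequency outcome. On that reading, day-0 episodes are part of the total.

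**Step 3: direction.** Let knowledge of the arm raise the control group's t0 score by δ (higher = worse, in SD units), with no true treatment effect and post-baseline values untouched.

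| Use of t0 | Bias in control minus acupuncture | Favours |
|---|---|---|
| Subtracted (change from t0) | −δ | control |
| Covariate with slope r | −r × δ | control |
| Day 0 counted in the six-day total | + the extra day-0 episodes reported | acupuncture |
| Days 1–5 only, t0 not used | 0 | neither |

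If control patients instead reported better at t0, every sign would reverse. A repeated measures model that contrasts later days with t0 behaves like the first row.

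**Step 4: size, by assumption only.** The documents give no value for δ or r, so this only shows how the bias scales. Assume δ = 0.1 to 0.3 SD, r = 0.3 to 0.7, one pairwise comparison, two-sided 5 %, equal SDs at t0 and follow-up, and no true effect. The number per arm comes from the sample size section: 192 / 4 = 48 evaluable (and 192 / (1 − 0.20) = 240, which reproduces the stated total).

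- Change from t0: bias δ = 0.1 to 0.3 SD; SE = √(2(1 − r)) × √(2/48). The rejection rate runs from about 7 % (δ = 0.1, r = 0.3) to about 48 % (δ = 0.3, r = 0.7).
- t0 as covariate: bias r × δ, from 0.3 × 0.1 = 0.03 to 0.7 × 0.3 = 0.21 SD; SE = √(1 − r²) × √(2/48). The rejection rate runs from about 5 % to about 30 %.
- Check of the upper corner for change: SE = √0.6 × 0.204 = 0.158; 0.3 / 0.158 = 1.90; probability of exceeding 1.96 is about 0.48.

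In the scenario of Step 3, the excess rejections in both analyses point against acupuncture.

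**The case against.** The strongest reply has four parts.

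1. **The exposed analyses are mostly not planned.** The Statistical analysis section names Kruskal-Wallis, chi-square, ANOVA and repeated measures. It names no change score and no baseline-adjusted model, and the primary count has no baseline subtracted. This stands. A reader might infer that change from baseline, covariate adjustment and repeated measures are all biased. The documents support only that they could be, if t0 is used in them.
2. **The moment of disclosure is not stated.** The article does not say that the patient hears the arm before answering the t0 questions; assignment and baseline evaluation are joined in one sentence on one day. This stands as a limit: the t0 values can be affected, which is not the same as showing that they are.
3. **Not every t0 measure is a pure self-report.** Nausea and vomiting are graded by CTCAE, the electrogastrogram is an instrument reading, and the Discussion says a blinded assessor administers and collects all outcomes. This narrows the point to the patient-reported measures and does not remove it.
4. **Open-label reporting affects days 1 to 5 anyway.** This is true, and reordering day 0 does not cure it. Whether day 0 belongs in the total at all is a separate question.

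Two further inferences are tempting. One is that patients could withdraw on learning their arm before any baseline exists; the -t1 tick for baseline variables contradicts that wording, since only the outcome baselines are missing before allocation. The other is to express the bias as a share of the effect the trial is sized to detect. With 48 per arm, a two-sided 5 % test and 90 % power, one can derive 3.24 × √(2/48) = 0.66 SD, and an assumed shift of 0.2 SD would be 30 % of it. But the sample size section states no effect size, SD, endpoint or sidedness, so neither figure is the plan's own.

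**Conclusion.** The point holds as a matter of sequence. The article places the outcome baseline after assignment of unblinded patients, and nothing elsewhere puts a patient-reported baseline before allocation. Confidence in that is high.

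The size of any bias is unknown, and its sign depends on how t0 is used. The ranges in the working rest wholly on assumed shifts and correlations. A comparison restricted to post-baseline values is untouched by this route, so the documents do not support saying that the primary result is biased. The matter should be fixed because the remedy is simple and a missed pre-allocation baseline cannot be collected later; it is not a defect that invalidates the trial.

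**What to change.** **Patients still to be enrolled.** Change the Randomization section so that the evaluator completes all t0 outcome measures before the random number and group are obtained from the website. Split the t0 column of Table 2 so that these assessments stand before allocation. If sites already work in this order, the change is only to correct the sentence and the table.

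**Patients already enrolled.** Recruitment began in June 2015 and is described as continuing. Record for each patient whether the t0 measures preceded or followed allocation. Where they followed, base the between-arm comparison on days 1 to 5, without t0 as reference or covariate. Do not exclude these patients: under the order as written, exclusion could remove everyone enrolled so far.

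**Cost.** A revised sentence, a revised table and an instruction to site staff. All steps already fall on day 0, so no visit is added, and the sample size does not change. The web system need not be altered, because staff can simply request the number after the assessments are done. For the patients already enrolled, the added work is retrieving the order of the two steps.
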